**Phase 2**

In **Phase 2** of this study (Aim 3), the investigators will:

- conduct a prospective evaluation of whether proactive intervention by the Hypoglycemia Champion (augmented usual care) is associated with better diabetes regimen safety among KPNC members at high risk of hypoglycemia compared to usual care (control) [Aim 3].

**Aim 3 –Conduct a prospective evaluation of whether proactive intervention by the Hypoglycemia Champion APM (i.e., assignment to augmented usual care group) is associated with better diabetes medication regimen safety among KPNC members at high risk of hypoglycemia compared to usual care (control).**

- Randomly assign eligible patients to receive proactive intervention by the HC APM (augmented usual care group) for comparison to data-only patients receiving usual care. All eligible patients will be managed according to the regionally disseminated HOAP as new standard of care). All medical decisions for all patients (augmented usual care and usual care) are made by each member’s medical care team responsible for his or her care (not by study personnel).
- **Primary Outcome:** Proportion of high-risk patients prescribed safer diabetes regimens (discontinuation at 6 months compared to pre-baseline of sulfonylureas, mealtime [rapid-/short-acting], or mixed insulin) comparing study participants (augmented usual care) to data-only patients (usual care controls). The study hypothesis is that more study participants will be prescribed safer diabetes regimens compared to data-only patients. Baseline pharmacy dispensing data and medication discontinuation orders during follow up will be collected directly from EHR/Clarity tables.
  - i. As researchers, patients will not be contacted directly at any time.
  - ii. All care will be delivered under approved protocols by KPNC clinicians.
  - iii. All evaluation data related to clinical outcomes will be collected directly from the medical record of usual care.
- **Secondary Outcomes:** the investigators will also examine differences between study participants and data-only patients in glucagon prescribing, CGM use, hypoglycemia on the

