patient's problem list, HbA1c<8% (HEDIS-defined glycemic control metric), and ED visits or hospitalizations for hypoglycemia based on primary diagnosis. The study hypothesis is that study participants will have more glucagon prescribing, CGM use, and inclusion of hypoglycemia on the problem list, with stable glycemic control (HbA1c<8%), and fewer ED visits or hospitalizations for hypoglycemia. The investigators will also conduct Heterogeneity of Treatment Effect (HTE) analyses by age (<75 vs. ≥ 75 years), enrollment criterion (hypoglycemia prediction algorithm vs ED/hospital hypoglycemia admission), and race/ethnicity.

Assess whether this study involves a clinical trial. Clinical trial means a research study in which one or more human subjects are prospectively assigned to one or more interventions (which may include placebo or other control) to evaluate the effects of the interventions on biomedical or behavioral health-related outcomes.

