**Phase 2**

Eligibility criteria for Aim 3 (study participants and data-only patients) will include patients with type 2 diabetes (T2D) at high risk for hypoglycemia, including those 1) designated as “high-risk” by the existing hypoglycemia risk stratification tool[1, 2] developed by the investigator team and currently implemented into Health Connect, or 2) who have had an ED visit or hospitalization for hypoglycemia (as primary or principal diagnosis, respectively) in 6 months prior to cohort baseline (date of enrollment in cohort).

No exclusion criteria.

- Describe how individuals will be screened for eligibility.

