**Aim 2**

Months 2-4: Workflow/clinical pathway will be developed by PIs.

**Phase 2**Aim 3

Months 5-6:

- Develop procedures and metrics for outcome evaluation
- Identify eligible patients (N=200)(have a high hypoglycemia risk score or a recent ED visit or hospitalization for hypoglycemia); randomly select study participants and data-only patients (matched sample)
- Collect baseline EMR data on study participants and data-only patients

Months 7-12:

- HC APM conducts outreach to study participants for assessment and evaluation; provides hypoglycemia intervention to study participants.

Months 13-21

- Collect outcome data from EMR for study participants and data-only patients.

Months 21-24

- Analyze data and draft manuscript

- Procedures to monitor subjects for safety, including who will review the data and at what frequency for safety issues.

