**Phase 2**

Data collected from study participants and data-only patients

- Prescribing orders and pharmacy dispensing of medications including
- Durable medical equipment orders and dispensing of continuous glucose monitor devices and supplies
- Relevant lab results (e.g., HbA1c)
- ED visits or hospital admissions for hypoglycemia
- Hypoglycemia on the problem list
- Visit notes

- The duration of an individual subject's participation in the study.

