**Phase 2**

Statistical Design: The primary analysis for Aim 3 will be an intent-to-treat analysis using chi square tests and binomial regression. For the primary outcome, differences in the proportion of patients prescribed safer diabetes regimens (i.e., discontinuation of sulfonylureas, mealtime or mixed insulin) will be assessed at 6 months in the treatment vs. control arms. For the secondary outcomes, differences will be assessed in the proportion of patients who had an ED visit or hospitalization for hypoglycemia within 6 months, were prescribed CGM or prescribed glucagon, and were in glycemic control (HbA1c<8%) between the 2 study arms. The investigators will perform exploratory Heterogeneity of Treatment Effect (HTE) analyses for age, race and enrollment criterion (see above) by testing for statistical interactions with the exposure (treatment arm).

- When applicable, the power analysis.

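### The CGM, glucagon and problem-list outcomes are not defined relative to baseline, and no use of baseline status is specified in their analysis

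*Supplement*

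**What the plan says.** All references are to the version dated January 27, 2025.

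- **Outcomes (Section 4, Secondary Outcomes).** The hypothesis is that participants will have "more glucagon prescribing, CGM use, and inclusion of hypoglycemia on the problem list". CGM use and problem-list inclusion are worded as states, which a patient can already be in on the day of enrollment.
- **Analysis (Section 9b, Statistical Design).** The comparison is of proportions who "were prescribed CGM or prescribed glucagon". The 6-month window is attached to ED visits and hospitalizations, and not clearly to prescribing. The problem list is not mentioned in this paragraph.
- **Method (Section 9b).** The primary analysis is an "intent-to-treat analysis using chi square tests and binomial regression". No covariates are named. Baseline variables appear only in exploratory interaction tests for age, race and enrollment criterion.
- **Eligibility (Section 5b).** "No exclusion criteria". One of the two entry routes is a recent ED visit or hospitalization for hypoglycemia.
- **Data (Section 9a).** The schedule has the team "Collect baseline EMR data on study participants and data-only patients". The list of data items covers prescribing, CGM orders and dispensing, and "Hypoglycemia on the problem list".
- **Contrast.** The primary outcome is tied to baseline: "discontinuation at 6 months compared to pre-baseline of sulfonylureas, mealtime [rapid-/short-acting], or mixed insulin". These three secondary outcomes are not.

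**The concern.** A high-risk cohort with no exclusions may well include patients who already have a CGM, a glucagon prescription or a problem-list entry. If a renewal or a standing entry counts as an event, those patients raise the proportion in both arms together and leave less room for a difference. The outcome then mixes uptake during follow-up, which the Hypoglycemia Champion is meant to change, with status at entry, which the Champion cannot change.

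There are two consequences. The reported difference understates the effect on uptake. The variation due to baseline status stays in the standard error, although the data that would remove it are already being collected. Leaving the rule open also means that new or any could be chosen after the outcome data have been seen.

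**Working it through.** **Is there a figure to reproduce?** The plan gives none for these outcomes: no expected rates, baseline prevalence or power. Its only sample-size figure, 43 per arm in Section 9b, is for the primary outcome and does not bear on this point.

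**Inputs from the plan.** 200 patients, 100 per arm.

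**Inputs assumed.** Two-sided alpha of 0.05 (not stated in the plan). Uptake among patients without the item t = 35% with the Champion and c = 15% in usual care. Baseline prevalence b varied from 0 to 50%. Every patient with the item at baseline keeps it and counts as an event.

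**Formulas.**
- All-patient proportions: P1 = b + (1 − b)t and P0 = b + (1 − b)c
- All-patient difference: P1 − P0 = (1 − b)(t − c)
- Baseline non-users: 100(1 − b) per arm, difference t − c

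Example at b = 20%: P1 = 0.20 + 0.80 × 0.35 = 0.48 and P0 = 0.20 + 0.80 × 0.15 = 0.32. The difference is 0.16, against 0.20 among non-users.

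**Exact power of the chi-square test.**

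| b (assumed) | P1 vs P0 | Difference, all patients | Power, all patients unadjusted | Non-users per arm | Power, non-users |
|---|---|---|---|---|---|
| 0% | 35.0% vs 15.0% | 20 points | 91% | 100 | 91% |
| 5% | 38.2% vs 19.2% | 19 | 85% | 95 | 90% |
| 10% | 41.5% vs 23.5% | 18 | 78% | 90 | 88% |
| 20% | 48.0% vs 32.0% | 16 | 65% | 80 | 85% |
| 40% | 61.0% vs 49.0% | 12 | 42% | 60 | 74% |
| 50% | 67.5% vs 57.5% | 10 | 31% | 50 | 65% |

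**Sensitivity to the uptake rates (normal approximation, b = 30%).** Power for all patients against non-users is 51% and 74% for uptake of 40% vs 20%, 52% and 68% for 50% vs 30%, and 51% and 85% for 30% vs 10%.

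**What stratifying recovers (b = 20%).**
- Unadjusted standard error: √[(0.48 × 0.52 + 0.32 × 0.68)/100] = 0.0684, so difference/SE = 0.16/0.0684 = 2.34.
- Stratified by baseline status: 0.80 × √[(0.35 × 0.65 + 0.15 × 0.85)/80] = 0.0533, so 0.16/0.0533 = 3.00.
- Non-users only: SE = √[(0.35 × 0.65 + 0.15 × 0.85)/80] = 0.0666, so 0.20/0.0666 = 3.00.

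Stratification keeps the 16-point all-patient difference but recovers the precision. The variance falls by a factor of (0.0684/0.0533)² ≈ 1.65 at b = 20%, and by about 2.3 at b = 40%.

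**A remedy that does not work.** Under these assumptions all baseline users are events in both arms. A main-effects binomial model with an identity link forces one common risk difference on users and non-users, and fitted probabilities may not exceed 1. Fitted to the expected data, it gives a risk difference of about 10 points at b = 20% and about 0 at b = 40% and 50%. The log-link version gives a risk ratio of about 1.00 at all three values. Simply adding baseline status to such a model is therefore worse than the unadjusted test.

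**Primary outcome.** At the planned 60% vs 20% with 100 per arm, exact power is above 99.9%, so added precision matters little there.

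**The case against.** The strongest reply is that the documents nowhere say prevalent users are counted. Being prescribed CGM or glucagon, listed just after an outcome with a 6-month window, can be read as a new order in follow-up. A reader might infer from the status wording in Section 4 that existing users are events. That is plausible but not stated, so the defect is an undefined outcome.

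A reader might also infer that nothing is adjusted for baseline. The plan does not say so. Binomial regression is named without a covariate list, and the interaction models would normally carry age, race and enrollment criterion as main effects. The controls are also called a matched sample, with the matching variables unnamed. What can be said is that no use of baseline status is specified for these outcomes.

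Three further points stand. The size of the loss rests on assumed inputs and is nil at b = 0. Under random allocation, chance imbalance in baseline status is already reflected in the standard error, so there is no bias. Continuation of CGM or glucagon need not be complete or equal between arms, and a new-user analysis would miss an effect on it.

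The reply does not remove the need for a rule. On the new-order reading the plan still lacks a look-back and a window for prescribing, and the problem-list outcome still has no stated analysis.

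**Conclusion.** The point holds as a gap in definition and analysis for three secondary outcomes. The plan does not place CGM, glucagon and problem-list outcomes relative to baseline, and it does not specify any use of the baseline status it collects.

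If prevalent users are counted without adjustment, the difference shrinks by (1 − b). Under the assumed 35% vs 15% uptake, power drops below that of the smaller non-user analysis at every non-zero prevalence examined: by 10 percentage points at b = 10%, 20 at b = 20% and 32 at b = 40%. The documents cannot show which of these applies.

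It would be tempting to extend the criticism to the primary outcome. The documents do not support that as a material fault, since that outcome is already defined against pre-baseline and has ample power at the planned rates. Adjusting it is optional.

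**What to change.** In Section 9b, Statistical Design:

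1. For CGM, glucagon and the problem list, choose one of two definitions before outcome data are examined:
   - a new prescription or entry during the 6-month follow-up, among patients without one in a stated baseline look-back; or
   - status in all patients, with a risk difference stratified by baseline status (Mantel-Haenszel, or standardized from a logistic model).
2. Do not handle baseline status through a main-effects identity- or log-link binomial model.
3. Add the problem-list outcome to the analysis paragraph.
4. Name any covariates used in the binomial regression.

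The cost is a few lines of plan and code. The relevant items are already on the data-collection list, and baseline extraction is planned in both arms. The drawback of the new-user definition is that it uses fewer than 200 patients if any have the item at baseline, and it says nothing about continuation among existing users. The stratified analysis keeps everyone, but its difference remains diluted by (1 − b) and should be reported alongside the baseline prevalence.

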**Phase 2**

There will be no recruitment. All patients will already be receiving usual care from an APM.

- For study participants, the HC will communicate with each participant's provider (usual APM or physician) to coordinate care; the study participant will receive proactive intervention by the HC as an augmentation to their usual care.
- For the data-only patients, there will be no contact.

Indicate whether you will openly recruit using advertisements, websites, flyer, or brochures. (Upload the final versions of all recruitment materials to your submission to the IRB.)

N/A

Indicate if you plan to do targeted recruitment using existing records or referral. Please submit final versions of all referral emails/scripts.

N/A

Describe, by position/title, who will be recruiting and enrolling participants (providing the specific names of research team members is not necessary).

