**Phase 2**

APM will routinely monitor study participants for safety and report any concerns to the Investigator.

- Procedures performed to lessen the probability or magnitude of risks.

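### The only between-arm check on loss of glycemic control (HbA1c<8%) rests on routinely ordered tests, with no time point and no rule for untested patients, while only one arm gets added outreach

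*Supplement*

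**What the plan says.** All references are to the January 27, 2025 version of the protocol.

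- **Outcome.** Section 4 lists the secondary outcomes: glucagon prescribing, CGM use, hypoglycemia on the problem list, "HbA1c<8% (HEDIS-defined glycemic control metric"), and ED visits or hospitalizations for hypoglycemia. The hypothesis for the participants is more of the first three, "with stable glycemic control (HbA1c<8%), and fewer ED visits or hospitalizations for hypoglycemia".
- **Analysis.** Section 9b will compare the proportions who "were in glycemic control (HbA1c<8%) between the 2 study arms". The same paragraph sets the primary outcome at 6 months and counts hypoglycemia events within 6 months, but gives HbA1c no time point. It has no rule for choosing among several values and none for patients without a value.
- **Data source.** Section 4: "All evaluation data related to clinical outcomes will be collected directly from the medical record of usual care". Section 9a lists the laboratory item as "Relevant lab results (e.g., HbA1c").
- **Contact.** Section 9a, months 7-12: "HC APM conducts outreach to study participants for assessment and evaluation". Section 6: "For the data-only patients, there will be no contact". Sections 6 and 7b also say that every patient already has usual APM care and that the data-only patients keep it.
- **Safety review.** Section 9a: "APM will routinely monitor study participants for safety and report any concerns to the Investigator". Section 14 answers the question on data monitoring as not applicable.

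**The concern.** The intervention aims to have sulfonylureas and mealtime or mixed insulin discontinued, and section 9b expects a safer regimen in about 60% of one arm and 20% of the other. The obvious counter-risk is worse glycemia. HbA1c<8% is the only listed outcome that can show it: mean HbA1c, change in HbA1c and hyperglycemia events are not compared between arms, and safety monitoring covers one arm only.

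That single measure exists only where someone ordered a test. If the added outreach leads to more testing in its arm, who has a result depends on allocation, and randomization no longer protects the comparison. Because the hoped-for result is stability, a bias that conceals a loss would look like success. With no time point, a value drawn early in follow-up, before any regimen change, could also stand as the outcome.

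**Working it through.** The plan states no figure for the HbA1c outcome, so there is none to reproduce. Its sample-size statement concerns the primary outcome only and does not bear on this point.

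**Inputs.** From section 9b: 100 patients per arm. The documents give neither control rates nor testing rates, so those below are assumptions. Let p be the true proportion with HbA1c<8% and t the proportion tested; HC is the Hypoglycemia Champion arm and C the control arm.

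**Handling 1: untested patients counted as not in control.** If testing does not depend on control status, observed proportion = t × p. Take p = 0.50 (HC) and 0.60 (C), a true loss of 10 points.

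| Tested, HC / C | Observed HC | Observed C | Difference |
|---|---|---|---|
| 90% / 90% | 0.9 × 0.5 = 45% | 0.9 × 0.6 = 54% | -9 points |
| 90% / 80% | 45% | 0.8 × 0.6 = 48% | -3 points |
| 90% / 70% | 45% | 0.7 × 0.6 = 42% | +3 points |

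The loss disappears when t(HC)/t(C) reaches p(C)/p(HC) = 0.60/0.50 = 1.20. Over control-arm rates of 60-80% and losses of 5-15 points, this ratio runs from 0.80/0.75 = 1.07 to 0.60/0.45 = 1.33.

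**Handling 2: untested patients dropped.** Observed proportion = p·s1 / (p·s1 + (1-p)·s0), where s1 and s0 are the testing rates among controlled and uncontrolled patients. Keep p as above and test 90% of the HC arm regardless of status, so its observed rate is the true 50%.

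- Controls tested more when uncontrolled (s1 = 0.6, s0 = 0.9): 0.36 / (0.36 + 0.36) = 50.0%. The difference is 0 and the loss is hidden.
- Controls tested more when controlled (s1 = 0.9, s0 = 0.6): 0.54 / (0.54 + 0.24) = 69.2%. The difference is -19.2 points and the loss is exaggerated.

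With true rates of 60% (HC) and 70% (C), the same two patterns give -0.9 and -17.8 points.

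**Best-case/worst-case bounds.** Suppose no true difference: p = 60% and 90% tested in both arms. The worst case for HC is 54% against 54% + 10% = 64%, or -10 points. With 90% and 70% tested, the bounds run from 54% - 72% = -18 to 64% - 42% = +22 points. The bounds are informative but too wide to serve as a gate.

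**The case against.** **The control arm is not without contact.** A reader might infer that data-only patients are never contacted. The documents do not support that: section 6 excludes contact by the study, while sections 4, 6 and 7b give these patients their usual APM and HOAP-based care. The contrast is usual care against usual care plus outreach, so the testing gap may be small. This stands.

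**Differential testing is not documented.** No testing rate is given, and nothing says that the Champion orders HbA1c. In a diabetes registry population within a system attentive to HEDIS measures, testing may be high in both arms. This also stands; the 70% and 80% figures are illustrations.

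**The direction is not fixed.** A reader might infer that the bias must favor the intervention. That holds only under the first handling, which the plan does not adopt. Section 9b attaches intent-to-treat to the primary analysis, and that principle does not by itself classify a patient without a result. The HEDIS label points to an outside definition that the protocol does not reproduce.

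**This is detail for a separate analysis plan, on one secondary outcome.** In part. Precision is limited anyway: even with complete testing, 100 per arm has only about 29-37% power for a true 10-point loss (control rate 60-80%, two-sided 5%), so a non-significant result could not establish stability. But section 9b is where this protocol is asked for its data analysis plan, and the issue goes beyond a missing detail. The design leaves ascertainment of its sole glycemic-harm measure open to differ by arm.

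**Conclusion.** The point holds as a risk, not as a demonstrated bias. HbA1c<8% is the only between-arm check on loss of control, it relies on routinely ordered tests, and it lacks a time point and a rule for untested patients. If the outreach arm is tested more often, which is plausible but not stated, a true 10-point loss could appear anywhere from a 3-point loss to a 3-point gain under the first handling with the assumed testing rates. Under the second it could vanish or nearly double. The outcome is secondary, so the primary result is unaffected. It should still be corrected, because no other planned outcome could contradict a statement that control stayed stable.

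**What to change.** In section 9b:

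1. Define the outcome as the last HbA1c in a fixed window around month 6, identical in both arms and excluding values from early follow-up.
2. Report by arm the proportions with HbA1c<8%, HbA1c of 8% or more, and no test in the window. The third category gives the testing rates directly.
3. Compare control between arms with adjustment for baseline HbA1c, under both handlings: untested counted as not in control, and untested excluded. Neither is safe alone, so show both. The binomial regression already named can carry this.
4. Give best-case/worst-case bounds as a sensitivity analysis, not as a condition for concluding; as a condition they would block a finding of stability even with no harm and equal 90% testing.
5. Interpret any statement of stable control in light of the testing rates by arm.

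The cost is a few lines of text and minor extra analysis of laboratory data already being collected. The downside for the sponsor is a possibly less favorable or more qualified statement about stable control.
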